**Safety monitoring**

Participants undergo scheduled clinical and biochemical monitoring.

### Quality of life (QOL) measurement

During patient interviews, a validated Chronic Liver Disease Questionnaire (CLDQ) is being administered to assess quality of life (QOL).
^
33
^ The copyright license for the English version of the questionnaire is being obtained from the authors. The QOL questionnaire is being completed both pre-transplant and at the one-year post-transplant follow-up. Patients are completing the questionnaire in either Malayalam or English.

The CLDQ includes six domains:
•
**Abdominal symptoms (AB)**: Items 1, 5, 17•
**Fatigue (FA)**: Items 2, 4, 8, 11, 13•
**Systemic symptoms (SY)**: Items 3, 6, 21, 23, 27•
**Activity (AC)**: Items 7, 9, 14•
**Emotional functions (EM)**: Items 10, 12, 15, 16, 19, 20, 24, 26•
**Worry (WO)**: Items 18, 22, 25

The CLDQ overall score is the sum of the scores from each domain, ranging from 0 to 203. Lower scores indicate poorer quality of life.

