### Secondary outcomes

•Assessment of biochemical markers (Liver function tests, metabolic profile, CRP, tacrolimus levels).•Molecular markers (fibroblast growth factor 19 (FGF-19), transforming growth factor β (TGF-β) level, Cytokeratin 18 level, Serum autotaxin level, Bile Salt Export Pump levels (BSEP), Plasma bile acid levels.•Biopsy-proven acute or chronic rejection.•Incidence of biliary complications.•All-cause mortality.•Any adverse events.•Death due to acute or chronic rejection.•Quality of life.

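### The CLDQ domain map lists 27 items, but the stated total range of 0 to 203 cannot be obtained from 27 items with a common whole-number maximum

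*Protocol article*

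**What the plan says.** "Quality of life" is listed in the protocol article under Secondary outcomes. The section Quality of life (QOL) measurement names the Chronic Liver Disease Questionnaire (CLDQ) as the instrument, given before transplant and at one year, in Malayalam or English.

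That section sets out the scoring. It says "The CLDQ includes six domains" and gives the item numbers for each. Fatigue, for example, has "Items 2, 4, 8, 11, 13", systemic symptoms has "Items 3, 6, 21, 23, 27" and emotional functions has "Items 10, 12, 15, 16, 19, 20, 24, 26". It then gives the total and its range, "The CLDQ overall score is the sum of the scores from each domain, ranging from 0 to 203", and the direction, "Lower scores indicate poorer quality of life".

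The article states neither the number of items on the form nor the response scale per item. No other section gives a different item list or range.

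**The concern.** The total is defined as the sum of the domain scores, so the domain map alone fixes which items count and how high the total can go. The map and the printed range disagree, so at least one part of the scoring rule is wrong as written.

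What is at stake depends on which part is wrong:

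- If the forms hold more items than the map, following the map leaves those items out of their domains and out of the total.
- If the forms hold 27 items, the printed maximum may be unreachable, and a score read against it looks worse than it is. With a maximum of 7 per item, a perfect score of 189 would read as 189/203 = 93%.

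A reader of the article cannot tell which case applies.

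**Working it through.** **Inputs**, all from Quality of life (QOL) measurement:

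| Domain | Item numbers | Count |
|---|---|---|
| Abdominal symptoms | 1; 5; 17 | 3 |
| Fatigue | 2; 4; 8; 11; 13 | 5 |
| Systemic symptoms | 3; 6; 21; 23; 27 | 5 |
| Activity | 7; 9; 14 | 3 |
| Emotional functions | 10; 12; 15; 16; 19; 20; 24; 26 | 8 |
| Worry | 18; 22; 25 | 3 |
| **Total** | | **27** |

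Put in order, these are exactly the numbers 1 to 27, with no gap and no repeat.

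**Step 1: try to reproduce the stated maximum.** For a sum score, maximum = number of items x maximum per item. From 27 items, 203/27 = 7.52, with remainder 14. A maximum of 7 per item gives 27 x 7 = 189, and a maximum of 8 gives 27 x 8 = 216. The stated 203 lies between the two, so it is not reproduced.

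**Step 2: find what would give 203.** The only factors of 203 are 1, 7, 29 and 203, so the plausible source is 29 items with a maximum of 7. That is two items more than the map assigns. With a maximum of 7, the listed items fall short by 203 - 189 = 14 points, which is two items' worth, or 14/203 = 6.9%.

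**Step 3: check both ends of the range.** Minimum = number of items x minimum per item. The item scale is not stated, so several are shown:

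| Item scale (assumed) | 27 items | 29 items |
|---|---|---|
| 1 to 7 | 27 to 189 | 29 to 203 |
| 0 to 7 | 0 to 189 | 0 to 203 |
| 0 to 6 | 0 to 162 | 0 to 174 |
| 1 to 8 | 27 to 216 | 29 to 232 |
| 0 to 8 | 0 to 216 | 0 to 232 |

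If each domain were scored as the mean of its items on a 1 to 7 scale, the sum of six domains would run from 6 to 42.

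No scale in the 27-item column gives 0 to 203. In the 29-item column only 0 to 7 does, and that is an eight-point scale. With 29 items on a seven-point scale, one end is still wrong: 1 to 7 gives a minimum of 29, and 0 to 6 gives a maximum of 174.

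**The case against.** The best defence is that this is a slip in a condensed article about an established instrument. The section calls the questionnaire validated and cites a source. Data Availability lists the English and Malayalam questionnaires and the data collection form as deposited files, and the actual scoring may follow those.

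The practical effect may also be small. Quality of life plays no part in the endpoint under Primary outcomes or in the calculation under Sample size. The article uses no cut-off or responder threshold tied to 0 or 203. If only the range is misprinted, the between-group t-tests under Statistical analysis are unchanged. If items are left out, they are left out in both arms, which narrows what is measured but does not by itself favour either drug.

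All of this stands as a limit on the size of the problem. It does not remove the contradiction, because the article prints a map, a summation rule and a range that do not fit together.

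Two stronger readings are tempting, and the article supports neither:

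- **Two answers are being collected and discarded, and a domain is under-scored.** This follows only if the forms hold 29 items and the printed map is the one in use. The forms are not shown, and the error may equally lie in the figure of 203. If two items are missing, the article does not say whether they belong to one domain or two.
- **The range of 0 to 203 shows a form with 29 seven-point items.** The maximum suggests 29 items, but the minimum does not fit seven-point scoring.

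Unequal domain sizes might also prompt a call for domain means. That is a reporting preference; a sum score is not an error.

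**Conclusion.** The scoring rule is wrong as written. The mismatch between 27 items and a maximum of 203 assumes only that all items share one whole-number maximum; nothing in the article suggests otherwise.

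The figures of 189, 14 points and 6.9% rest on a further assumption, a maximum of 7 per item, inferred from 203 = 29 x 7. The corrected minimum of 27 or 29 rests on items being scored from 1 to 7. The article does not show which element is at fault, nor that any questionnaire has been mis-scored.

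The correction should be made, but its reach is limited to the quality-of-life secondary outcome.

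**What to change.** 1. Compare the printed domain map with the English and Malayalam forms in use, and confirm that both forms have the same number of items.
2. Assign every item on the form to a domain.
3. State the response scale per item.
4. Correct both the minimum and the maximum of the total to match the item count and scale.
5. If the forms hold more items than the map, and any questionnaires were scored with the 27-item map, re-score them from the item answers already collected. Otherwise no re-scoring is needed.

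The cost is one corrected scoring table and, at most, one re-run of the scoring. No new data are required. Because Study status describes the trial as still recruiting, the correction can be made before the final analysis.

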### Sample size

The sample size was calculated based on a pilot study comparing the effect of obeticholic acid (OCA) and ursodeoxycholic acid (UDCA) on cholestatic injury in post-liver transplant patients. In the pilot study, the difference in alkaline phosphatase (5.131 ± 39.639 vs 12.496 ± 52.139) was observed between the two groups. With 80% power and 95% confidence, the minimum sample size required was determined to be 108 patients in each group, totaling 216 samples. We will be recruiting around 110 to 120 patients per arm. The calculation was based on the expected difference in ALP reduction between groups observed in pilot data.

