## Introduction

Liver diseases cause nearly 2 million deaths worldwide each year, with approximately 1 million deaths from cirrhosis complications and another 1 million from viral hepatitis and liver cancer, according to WHO estimates.
^
1,
2
^ Liver transplantation (LT) is recognized as the primary curative treatment, with success rates reaching 85% in the first year and 75% at 5 years post-transplantation.
^
3
^ In India, over 3000 liver transplants are performed annually. Despite the considerable expense associated with LT, it is considered cost-effective, especially for individuals in their prime years, who have many active work years ahead of them.
^
4,
5
^ However, post-transplant morbidity, particularly intrahepatic cholestasis, presents significant challenges.
^
6
^

Intrahepatic cholestasis is a major complication following liver transplantation, caused by multiple factors. Ischemia-reperfusion injury during organ retrieval and transplantation leads to cellular damage and postoperative cholestasis.
^
7,
8
^ Sepsis from infections worsen cholestasis through inflammatory responses.
^
9
^ Essential post-transplant drugs, including immunosuppressants and antibiotics, can interfere with bile formation, causing liver injury.
^
10,
11
^ Immunological reactions such as T-cell and B-cell-mediated rejection and lymphocytic cholangitis also contribute to cholestasis.
^
12
^ Surgical complications like stenosis or obstruction of the biliary and vascular anastomosis can also result in intra- and extrahepatic cholestasis.
^
13–
15
^

The absence of effective medicines limits the current medical therapy of cholestasis. Although its usefulness is questionable, many practitioners utilize ursodeoxycholic acid (UDCA) as a hepatoprotective drug.
^
15
^ It is usually administered for three months post-transplant at a dose of 10-15 mg/kg thrice daily. In 2016, the FDA approved obeticholic acid (OCA), a strong selective Farnesoid X Receptor (FXR) agonist, to treat primary biliary cholangitis (PBC) in conjunction with UDCA.
^
16,
17
^ Research has demonstrated that over 12 months, OCA, either in combination with UDCA or on its own, dramatically lowers levels of total bilirubin and alkaline phosphatase.
^
18,
19
^ In individuals with advanced liver disease, the FDA has cautioned against administering OCA at doses of 10–50 mg.
^
20

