**Allocation**

Participants are randomized in a 1:1 ratio using a computer-generated permuted block sequence. Allocation concealment will be ensured using sequentially numbered, sealed opaque envelopes opened by the study pharmacist on postoperative day two.

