## Expected results

We expect a significant reduction in cholestatic liver enzymes following LDLT in the OCA group compared to the UDCA group, with improvements observed from one month to subsequent time points (3, 6, and 12 months). We hypothesize that the potent mechanism of action of OCA will ameliorate cholestatic injury and enhance graft survival. Additionally, we anticipate a reduction in biliary complications, all-cause mortality, and an increase in quality of life for OCA-receiving patients. This may reduce long-term financial expenditure for patients. Given that there are currently no drugs to prevent damage to the transplanted liver, a positive outcome could be a significant advancement for the transplant population. If beneficial, this study could lead to the adoption of OCA as a standard of care following liver transplantation. If proven beneficial, this study could support the potential adoption of obeticholic acid (OCA) as a therapeutic option in the management of post-liver transplant cholestasis. Although regulatory approval for OCA in primary biliary cholangitis was withdrawn due to the lack of confirmatory clinical benefit, its distinct mechanism of action and the different pathophysiological context of post-transplant cholestasis warrant independent evaluation in this setting.

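### The stated 108 per arm does not follow from the printed pilot ALP values, which need about 621 per arm; 108 fits only the sum of the two means, so either a minus sign is missing (power about 80%) or the means were added in error (about 22%)

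*Protocol article*

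**What the plan says.** The Sample size section of the protocol article gives both the inputs and the result of its calculation. From a pilot study comparing obeticholic acid (OCA) with ursodeoxycholic acid (UDCA), it states that "the difference in alkaline phosphatase (5.131 ± 39.639 vs 12.496 ± 52.139) was observed between the two groups". It then says: "With 80% power and 95% confidence, the minimum sample size required was determined to be 108 patients in each group, totaling 216 samples". The planned intake is slightly larger: "We will be recruiting around 110 to 120 patients per arm". The effect size is described in these words: "The calculation was based on the expected difference in ALP reduction between groups observed in pilot data".

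Two other sections supply the rest of the set-up. Allocation: "Participants are randomized in a 1:1 ratio using a computer-generated permuted block sequence". The Statistical analysis section compares continuous variables between groups with an independent-sample t-test.

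Neither pilot mean carries a minus sign. The section does not say which mean belongs to which arm, in what unit or at what time point the values were taken, or whether a positive value is a fall or a rise.

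**The concern.** The section prints everything needed to repeat the calculation, and the repeated calculation gives a number nearly six times the stated one. A gap of that size cannot come from rounding or from the choice of formula.

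The stated power is the article's only justification for the size of the trial. If the printed values are right, the trial has far less than 80% power for the difference seen in its own pilot. If a sign has been lost, the size is sound, but the article misreports its pilot result and a reader cannot tell which arm improved. In both cases the printed line needs correcting, and the study is still recruiting, so this can be done before results are known.

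**Working it through.** **Inputs** (Sample size section unless noted)
- Pilot ALP: 5.131 (SD 39.639) and 12.496 (SD 52.139).
- Power 80%; 95% confidence, read as two-sided 5% (sidedness is not stated).
- 1:1 allocation (Allocation section); independent-sample t-test (Statistical analysis section).

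**Formula**, for two means with equal arms:

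n per arm = (z for 97.5% + z for 80%)² × (SD₁² + SD₂²) / d²

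- (1.960 + 0.842)² ≈ 7.849
- 39.639² + 52.139² = 1571.25 + 2718.48 = 4289.73 (pooled SD 46.31)
- Numerator: 7.849 × 4289.73 ≈ 33,670

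**Attempt to reproduce 108 from the printed difference**
- d = 12.496 − 5.131 = 7.365, so d² = 54.24
- n = 33,670 / 54.24 = 620.7, that is 621 per arm (622 by the exact noncentral t), against 108 stated.

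Variants that keep d = 7.365 and 80% power:

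| Variant | Two-sided 5% | One-sided 5% |
|---|---|---|
| Pooled SD | 621 | 489 |
| SD 39.639 only | 455 | 359 |
| SD 52.139 only | 787 | 620 |
| Average of the two SDs | 610 | 481 |
| One-sample or paired form | 228 to 394 | 180 to 310 |

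None comes near 108, and 90% power raises every figure. To obtain 108 from 7.365 the common SD would have to be about 19.3, less than half of either printed SD.

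**What does reproduce 108**
- d = 12.496 + 5.131 = 17.627, so d² = 310.71
- n = 33,670 / 310.71 = 108.4. Strictly this rounds up to 109 (110 by exact t), but 108 is plainly this number.
- Adding the means is arithmetically the same as taking the difference of two means of opposite sign.

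**Power at the planned sizes** (normal approximation, two-sided 5%)

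| Per arm | d = 7.365 | d = 17.627 |
|---|---|---|
| 108 | 21.4% | 79.9% |
| 110 | 21.8% | 80.6% |
| 120 | 23.3% | 83.8% |

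**Detectable difference at 108 per arm, 80% power:** 2.802 × √(4289.73 / 108) = 2.802 × 6.302 = 17.66.

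**The case against.** The strongest reply is that nothing is wrong with the calculation. The sum reproduces 108 so closely that opposite-signed pilot changes, with one minus sign lost in the article or in its conversion to text, are at least as plausible as a true addition error. On that reading the trial has about 80% power and the defect is a single character. This stands as an explanation, and it is why 22% must not be presented as the trial's established power. It does not remove the error in the line as it reads: one of the printed values or the stated power has to change.

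A second reply also stands. Both the article's calculation and this check concern a mean ALP difference, whereas the Primary outcomes section defines a responder proportion based on ALP and GGT. Neither 80% nor 22% is the power for that endpoint.

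Three stronger readings are tempting but not supported:
- **The pilot favoured UDCA, against the expected result.** The Expected results section says "We expect a significant reduction in cholestatic liver enzymes following LDLT in the OCA group compared to the UDCA group", and OCA is named before UDCA where the pilot is introduced. But the means are not labelled by arm and the meaning of a positive value is not given. If positive means a rise, the smaller first value would favour OCA; if a sign is missing, the direction is unknown.
- **The evaluable number will fall below 108.** The article excludes deaths within 30 days and losses to follow-up, but gives no loss rate. The Introduction describes transplantation generally "with success rates reaching 85% in the first year and 75% at 5 years post-transplantation"; the complement of that background figure is not a dropout rate for this trial. An intake of 110 leaves room for 2 losses (1.8%), and 120 for 12 (10%).
- **A null result would say almost nothing.** At 108 per arm the 95% confidence half-width is about 1.96 × 6.30 = 12.4, so an estimate near zero would still exclude differences beyond about 12.

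**Conclusion.** Wrong as written. The statement "the minimum sample size required was determined to be 108 patients in each group, totaling 216 samples" does not follow from the values printed beside it. As printed, those values need about 621 per arm, and 108 to 120 per arm give about 21% to 23% power for the pilot mean difference. Of the routes tried, only those that use the sum of the means, 17.627, come near 108.

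Either a sign is missing and the size is consistent with about 80% power, or the means were added and the stated power is wrong. The document does not decide between these. The conclusion assumes a two-sided 5% test of two independent means with the printed SDs; one-sided testing, other choices of SD and paired forms do not rescue the figure. It does not rest on any attrition rate, on the direction of the pilot result, or on the primary endpoint.

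**What to change.** Check the Sample size line against the published page and the pilot data, then correct it by giving the sign, arm, unit and time point of each mean.

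- **If the two means have opposite signs:** print the minus sign, say which arm improved, and keep about 80% power at 108 per arm for a difference of 17.6.
- **If the printed signs are right:** replace the 80% with about 22% for the pilot difference of 7.365, or state instead that 108 per arm detects a mean ALP difference of about 17.7 with 80% power.

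In both cases add a sentence saying that this power is for the mean ALP difference and not for the responder-proportion primary endpoint. If power after losses is also shown, label the loss rate as an assumption.

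The cost is a check of the pilot data and one rewritten paragraph, with a less favourable stated power if the second case applies. The correction needs no extra recruitment and no change in conduct.

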### Study status

The study is currently in the recruitment phase.

### Statistical analysis

•To compare the means of continuous variables between groups (Drug A vs Drug B), an independent sample t-test will be used at each time point.•To compare the changes in continuous variables from pre- (1 month) to post-transplant (3, 6, and 12 months), a paired t-test will be applied.•To compare the means of variables from baseline to subsequent time points within each group, repeated measures ANOVA will be used if significant. Repeated measures analysis will be used to assess longitudinal changes over time, and Bonferroni correction will be applied for multiple comparisons where appropriate.

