### Primary outcomes

The primary endpoint will be the proportion of patients achieving a ≥15% reduction in serum alkaline phosphatase (ALP) and gamma-glutamyl transferase (GGT) levels at 3, 6 and 12 months compared with the one-month post-transplant baseline between the two groups. ALP and GGT is assessed at 6 and 12 months to evaluate the trajectory and durability of response over time.

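### The 80% power and the listed tests belong to mean ALP, not to the declared primary endpoint, a responder proportion on ALP and GGT

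*Protocol article*

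**What the plan says.** Three sections of the protocol article bear on this.

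- **Primary outcomes:** "The primary endpoint will be the proportion of patients achieving a ≥15% reduction in serum alkaline phosphatase (ALP) and gamma-glutamyl transferase (GGT) levels", assessed "at 3, 6 and 12 months compared with the one-month post-transplant baseline between the two groups". Each patient is a responder or not. The text below Figure 1 defends the 15% threshold and says that it applies to both enzymes.
- **Sample size:** in the pilot, "the difference in alkaline phosphatase (5.131 ± 39.639 vs 12.496 ± 52.139) was observed between the two groups". The section continues "With 80% power and 95% confidence", "the minimum sample size required was determined to be 108 patients in each group, totaling 216 samples", and ends: "The calculation was based on the expected difference in ALP reduction between groups observed in pilot data". It gives no responder rate for either arm and does not mention GGT.
- **Statistical analysis:** for the two arms, "an independent sample t-test will be used at each time point", applied to means. The other methods are a paired t-test on change from month one and repeated measures analysis, with Bonferroni correction where judged appropriate. No method for comparing proportions is named here or elsewhere in the article.

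**The concern.** The endpoint, the sample size and the analysis should concern the same quantity. Here the endpoint is a proportion defined on two enzymes, while the other two concern the mean of a continuous measure, and the sample size uses one enzyme only.

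Two things are at stake. First, a reader will take 80% as the chance of detecting an effect on the primary endpoint, and the calculation does not support that. Second, the trial is open-label and recruiting. If a responder endpoint is declared while only tests of means are written down, either analysis could later be presented as the main result.

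**Working it through.** **1. The article's own figure.** Inputs from Sample size: means 5.131 and 12.496, SDs 39.639 and 52.139, 80% power, 95% confidence (taken as two-sided alpha 0.05).

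- Pooled SD = √[(39.639² + 52.139²)/2] = 46.313.
- Difference as printed = 12.496 − 5.131 = 7.365.
- n per arm = 2 × [46.313 × (1.960 + 0.842)/7.365]² ≈ 621, not 108.
- If the two pilot means had opposite signs, the difference would be 12.496 + 5.131 = 17.627, and n = 2 × [46.313 × (1.960 + 0.842)/17.627]² = 108.4, which agrees with 108 within rounding.

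Whether a minus sign was lost is a separate question for the sponsor. What matters here is that the inputs are means and SDs of ALP, so 108 is a sample size for means on any route.

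**2. What 108 per arm gives for the declared endpoint.** The article states no response rate, so the lower rate p₁ is assumed over 20% to 70%. The formula, without continuity correction, is

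n = [z₁₋α/₂ √(2p̄(1−p̄)) + z₀.₈₀ √(p₁(1−p₁) + p₂(1−p₂))]² / (p₂ − p₁)², with p̄ = (p₁ + p₂)/2.

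Worked example with p₁ = 0.40, p₂ = 0.59, p̄ = 0.495:

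- first term: 1.960 × √0.49995 = 1.386
- second term: 0.842 × √(0.2400 + 0.2419) = 0.584
- n = (1.386 + 0.584)²/0.19² ≈ 107.5, so 108 per arm.

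Smallest difference, in percentage points, detectable with 80% power at 108 per arm:

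| Lower response rate (assumed) | One visit, alpha 0.05 | Each of three visits, alpha 0.05/3 |
|---|---|---|
| 20% | 17.2 | 20.1 |
| 30% | 18.6 | 21.5 |
| 40% | 19.0 | 21.9 |
| 50% | 18.7 | 21.4 |
| 60% | 17.6 | 20.1 |
| 70% | 15.8 | 17.9 |

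At 120 per arm, the top of the recruitment range, the one-visit figures fall to between 15.1 and 18.0 points.

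**3. Power at 108 per arm for fixed differences** (one visit, alpha 0.05, same range of lower rates): 31% to 40% for 10 points, 60% to 76% for 15 points, and 84% to 96% for 20 points. Power for the responder endpoint may thus lie well below or above 80%, depending on assumptions that the article does not state.

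**4. The listed tests set against the endpoint.** The independent t-test compares arm means. The paired t-test looks at change in a continuous measure. The repeated measures ANOVA follows means over time within each group. None estimates or tests a difference in responder proportions. The Bonferroni statement is not tied to the three visits at which the primary endpoint is assessed.

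**The case against.** The strongest reply is that this is an article, and a statistical analysis plan may exist that names the test for the responder proportion. The analysis section limits itself to continuous variables and never labels the t-test as the primary analysis. Rejection, biliary complications and mortality have no named test either, which suggests a condensed list rather than a decision to analyse means. The sample size section is also open about its basis: it says that the calculation rests on ALP reduction and does not claim that 108 was derived for the responder endpoint.

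Much of this stands. A reader might infer that the trial has no prespecified test for its primary endpoint anywhere, or that the investigators intend to report a t-test on ALP as the main result. The article supports neither inference. It shows only that its stated methods do not fit its stated endpoint.

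A reader might also infer that the trial is underpowered for the responder endpoint, for instance by turning the pilot means and SDs into responder rates. That needs percent units and a normal distribution, and the article gives neither. Any shortfall found that way with the printed figures would also reflect the separate failure of 108 to follow from the printed difference, and could not be put down to the mismatch.

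The reply does not remove the conflict over power. The article states a sample-size basis and a power, and they concern a different quantity from the endpoint it declares.

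**Conclusion.** The point holds in this form: the 80% power stated for 108 per arm does not apply to the declared primary endpoint, and the analyses listed in the article would not test that endpoint.

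The documents do not show that 108 is too few. It is enough if the true difference in response is at least about 16 to 19 points at a single visit, or about 18 to 22 points with alpha split equally over three visits. These ranges rest on an assumed lower response rate of 20% to 70%, a two-sided 5% test, no continuity correction, and 108 evaluable patients per arm. The defect is that the article states no expected response rates or difference against which to judge the size.

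**What to change.** **Statistical analysis:** name one between-arm analysis of the ALP-and-GGT responder proportion, for example a risk difference with 95% CI. Either designate one primary visit or state how alpha is divided over 3, 6 and 12 months. Label the t-tests and repeated measures analyses of ALP and GGT as supportive.

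**Sample size:** say that 108 per arm was derived for mean ALP change. Then state what 108 per arm can detect for the responder endpoint, together with the control response rate assumed and the alpha used. With a 40% control rate and one visit at 0.05, for example, that is a rise of about 19 points. The figure should not appear without its rate.

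**Cost:** wording in two paragraphs and a few lines of code, with no change to recruitment or data collection. The downside is that the stated detectable effect becomes less favourable. The change should be made and dated before any comparison of outcomes by arm.
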